# Study Summary

**Title**

Defining the risk of renal function decline and cardiovascular disease among patients with chronic kidney disease stage 3: The Renal Risk in Derby (R2ID) Study.

**Protocol Version Number and Date**

Version 2.3

October 2013

**Short Title**

Renal and Cardiovascular Risk in CKD stage 3

**Methodology**

Long term observational study to assess risk factors.

**Study Duration**

Eleven years and 10 months. See section 3.1 for details.

**Study Centres**

Royal Derby Hospital

GP Practices within Southern Derbyshire CCG, North Derbyshire CCG

and Erewash CCG.

**Objectives**

To define the risk of kidney function decline in a cohort of patients with chronic kidney disease (CKD) stage 3.

To define the risk of cardiovascular disease in a cohort of patients with chronic kidney disease (CKD) stage 3.

**Number of Subjects/Patients**

1822

**Main Inclusion Criteria**

CKD stage 3 as defined by the K/DOQI classification (i.e. GFR 30-59ml/min/1.73m2 on 2 occasions at least 3 months apart)

Age >18 years

**Statistical Methodology and Analysis**

Descriptive statistics for baseline data.

Univariate and Multivariate analysis to investigate associations between CKD, cardiovascular disease and risk factors at baseline.

Cox regression analysis to investigate risk factors for CKD progression and cardiovascular events.

# 1. Introduction

The described research study will be conducted in compliance with the protocol, the Research Governance Framework, International Conference on Harmonisation Good Clinical Practice Guideline ICH/GCP, and all applicable Derby Hospitals NHS Foundation Trust Research Office requirements.

## Background

The introduction of estimated glomerular filtration rate (GFR) to assess renal function has identified large numbers of patients with previously undetected chronic kidney disease (CKD). It is clear from previous studies that there is considerable heterogeneity in the risk of decline in renal function among patients with similar levels of GFR. Patients therefore differ widely in their need for specialist referral and treatment. Epidemiological studies have identified multiple risk factors for CKD progression [1] but few have sought to define the risk in individual patients. Several attempts have been made to develop scoring systems to predict renal risk but these studies have largely been limited to patients with specific kidney diseases and have not been validated in more general populations of patients with CKD [2-4]. Chronic kidney disease is also associated with an increased risk of cardiovascular disease that in many cases’ exceeds the risk of developing end-stage renal disease (ESRD) [5]. It is not known, however, whether traditional cardiovascular risk factors are relevant in patients with CKD or whether cardiovascular risk assessment tools used in the general population are applicable to patients with CKD. Recent data indicates that the extent of advanced glycation end product (AGE) deposition in the skin is an important marker of cardiovascular risk among patients with CKD [6] and periodontal status has also been associated with risk of cardiovascular disease in those with and without CKD [7-10]. Preliminary data suggest that cardiovascular disease may also be a risk factor for CKD progression. Thus kidney and cardiovascular disease may exacerbate each other, leading to a vicious circle of progressive cardiovascular and renal decline.

# Study Objectives

## To define the risk of kidney function decline in a cohort of patients with chronic kidney disease (CKD) stage 3.

## To define the risk of cardiovascular disease in a cohort of patients with CKD stage 3.

## To develop a comprehensive description of patients with CKD stage 3, who are currently followed up by General Practitioners.

## To assess the management of patients with CKD stage 3 by General Practitioners compared with Renal Association Clinical Practice Guidelines.

## To develop care plans to improve the care of patients with CKD stage 3 within Primary Care.

## To assess the value of monitoring urine albumin to creatinine ratio (UACR), urine sodium and urine phosphate in the management of patients with CKD stage 3.

## To assess associations between CKD and a wide range of previously described risk factors.

# Study Design

## General Design

This is a long-term longitudinal observational cohort study.

Patients will be followed for 10 years. Clinical assessments will take place as described at baseline, 1 year and 5 years. After this patients will no longer be assessed clinically but outcome data with respect to the primary end points as well as survival will be collected. The Medical Research Information Service (MRIS) will (an arm of the NHS Information Centre), will be used to accurately track survival data of participants.

## Primary Study Endpoints

### The primary end-point for assessing progression of CKD will be doubling of serum creatinine or the need for renal replacement therapy from baseline to 5 years and 10 years.

### The primary end-point for assessing cardiovascular risk will be a cardiovascular event, defined as myocardial infarction of any type (fatal and non-fatal, NSTEMI and STEMI), need for coronary revascularisation, TIA, fatal and non-fatal CVA, need for peripheral revascularization, amputation for peripheral vascular disease, death due primarily to peripheral vascular disease or sudden cardiac death at any time during 5 and 10 years of follow-up.

## Secondary Study Endpoints

### GFR value at baseline, 1, 5 and 10 years.

### Urine protein to creatinine ratio at baseline, 1, 5 and 10 years.

### Blood pressure at baseline, 1, 5 and 10 years.

### All-cause mortality over 5 and 10 years.

# Methods

## Subject Selection and Withdrawal

**Inclusion Criteria**

### Age >18 years

- CKD stage 3 as defined by the K/DOQI classification (i.e. GFR 30-59ml/min/1.73m2 on 2 occasions at least 3 months apart)

**Exclusion Criteria**

- Inability to attend GP surgery
- Inability to provide informed consent

## Subject Recruitment and Screening

Patients with CKD stage 3 (as defined above) will be identified from General Practice CKD registers and biochemistry databases by participating General Practitioners. GPs will send out the patient information sheet and a letter of invitation to potential participants. Patients will be invited to set up an appointment for the initial assessment by telephoning a number at Royal Derby Hospital. If patients do not wish to participate they will be asked to confirm this by telephoning the same number. If no response has been received within 2 weeks a second letter may be sent.

Informed consent to participate in the study will be obtained at the time of the first visit by the researchers, this will include consent to certain identifiable information being passed on to the Medical Research Information Service. Patients will have at least 1 week to decide about participation.

No additional screening procedures will be required prior to entry.

Each patient will be assigned a unique study number that will be used to identify all data collected for the study. This will be allocated at the first study visit. A key of patient identity and study numbers will be kept on a password-protected Trust computer in a password-protected file. Any information passed onto the Medical Research Information Service will be in encrypted form.

A recruitment log will be maintained.

Details of participation in the study will be recorded in the patients’ GP records.

## Withdrawal of Subjects

Patients will be withdrawn only if they withdraw their consent.

### When and How to Withdraw Subjects

Patients who withdraw their consent will be removed from the study immediately. They will continue to receive routine care through their GP.

### Data Collection and Follow-up for Withdrawn Subjects

Patients who withdraw will be asked to allow data collected prior to the date of withdrawal to be retained for analysis. They will also be asked to allow outcome data, including clinical events and the results of any kidney function tests arranged by the GP, to be collected for future analysis. If a participant declines this their data will be deleted.

Patients who fail to attend for follow-up will be contacted by telephone to determine whether or not they are willing to continue. Patients without access to a telephone will be contacted by letter. If no response is received to two letters sent one month apart, the patient will be assumed to have been lost to follow-up.

## Prior and Concomitant Therapy

All current medications will be recorded. Patients will be asked if they have previously been treated with non-steroidal anti-inflammatory drugs, angiotensin-converting enzyme inhibitors or angiotensin receptor blockers for a period of 3 months or longer.

# Laboratory Assays

The following laboratory tests will be obtained at baseline, 1 year and 5 years. The majority of these tests form part of routine clinical care and would normally be performed annually by the General Practitioner. Tests marked with an asterix are not routine and will be performed by the researcher in a research laboratory. Participants will be asked not to eat meat for 12 hours prior to the blood tests (to avoid a potential effect on the creatinine assay).

- Urea and electrolytes
- Estimated GFR
- Calcium and phosphate
- Serum albumin
- Lipid profile
- Random blood glucose
- Bicarbonate
- Uric acid
- Full blood count
- Urine albumin:creatinine ratio (on three early morning specimens)
- Urine protein:creatinine ratio (on three early morning specimens)
- Urine sodium (on three early morning specimens)
- Urine phosphate (on three early morning specimens)
- 24h urine collection for measurement of urinary creatinine, protein, albumin, sodium and phosphate will be performed in a subgroup of 160 patients.
- High sensitivity C-reactive protein (CRP)
- ADMA (asymmetrical dimethyl arginine)
- Serum fibroblast growth factor 23 (FGF 23)*
- Serum 25 hydroxy-vitamin D
- Serum 1,25 dihydroxy-vitamin D
- Serum Parathyroid hormone
- Serum Cystatin C
- Serum free light chains
- Serum will be stored for future biochemical assays but these will not include genetic testing. This to allow testing of substances that may be identified as significant risk factors for renal or cardiovascular outcomes during the follow-up period. Serum will not be stored beyond the duration of the study.

# Randomisation

No applicable.

# Study Procedures

- Patients will be asked to complete an information sheet to provide demographic and medical history details prior to attending for the first study assessment. They will also be asked to complete a brief food frequency questionnaire to assess salt intake. Demographic and medical history will be assessed only at baseline. Current medication will be assessed at each study visit. The food frequency questionnaire will be repeated at each study visit. Medical history and treatment details will be checked against the GP records. If known, the cause of the CKD will be recorded and assigned a corresponding European Dialysis and Transplantation Association diagnostic code.
- The first part of the assessment (5-10 minutes) will comprise a patient interview to clarify details and complete any unfilled sections on the information sheet and food frequency questionnaire.
- A measure of socio-economic status with be derived from participants’ post code (Indicies of Multiple Deprivation(IMD) score)
- Quality of life will be assessed using the EQ5D questionnaire
- Functional status will be graded using the Karnofsky score
- Anthropomorphic Measurements (repeated at each study visit)
  - Height
  - Weight
  - Body Mass Index
  - Hip to waist ratio
  - Mid-upper arm muscle circumference
  - Hand grip strength
  - Gait speed
  - Sit to stand test
  - Blood pressure (seated; average of 3 readings recorded with an oscillometric device)
  - Peridontal assessment
  - Urine dipstick test
  - Non-invasive assessment of arterial pulsewave velocity (Viacorder, Skidmore Medical Ltd, Bristol, UK)
  - Non-invasive measurement of forearm skin autofluoresence as a measure of advanced glycation end product deposition (AGE Reader, DiagnOptics, Groningen, Netherlands)
- Venesection (repeated at each study visit)
  - 3 x 5ml clotted blood
  - 1x 3ml blood in EDTA
- Urine collection (repeated at each study visit)
  - 3 x 5-10ml first morning urine specimen

Each study visit is expected to last 30-40 minutes.

# Statistical Plan

Statistical advice has been sought from Derby Hospitals NHS Foundation Trust Statistician, [name].

## Sample Size Determination

The sample size was estimated based on two similar studies, one for predicting renal outcome in IgA nephropathy [4] and the other in patients with type 2 diabetes and nephropathy [3]. Based on these studies the smaller event rate was 12% and the smallest significant Hazard Ratio was 1.2. Therefore the total sample size for this study, using the Cox Proportional Hazards models with Power 80% and at significant level 5%, is 1968. Assuming death rate during the 5 years of 3% and drop out rate of 10% the final total sample is 2255. We plan to complete recruitment in 1 year and therefore aim to recruit approximately 190 participants per month. CKD stage 3 is estimated to affect at least 5% of the UK population. There should therefore be approximately 35,000 patients available for recruitment in Derbyshire.

A separate sample size estimate was performed for the sub-study comparing spot early morning urine biochemistry with that from 24hour urine collections. Based on previously published data, we calculated that a sample of 160 would allow us to show a correlation co-efficient of 0.9 with precision of the estimate of 0.03 at 80% power with a significance of 5% [7].

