## Statistical Methods

Basic demographic data will be retained on the anticipated small number of excluded patients as these form part of the at risk population. Descriptive statistics will be used to provide a summary of each of the variables collected at each time point. Multivariable linear regression analysis will be used to assess the effect of baseline variables as well as changes in these variables over the first 12 months on changes in blood pressure, proteinuria and glomerular filtration rate. Cox proportional hazards models will be used to identify independent baseline risk factors for CKD progression and cardiovascular events at 5 and 10 years. A similar method will be used to assess the possibility that changes in baseline variables from baseline to 12 or 24 months may be better predictors of CKD progression and cardiovascular events than baseline variables alone. Coefficients derived from Cox proportional hazards analysis for the independent determinants of CKD progression or cardiovascular events will then be used to produce a risk scoring system.

In a subgroup of 160 patients, assessment of proteinuria by urine protein to creatinine ratio versus albumin to creatinine ratio or 24h urinary protein will be assessed. Intraclass Correlation Coefficients will be used for comparing the three methods and Bland-Altman plots will be performed. 24 hour urinary protein will be the standard against which the other methods are compared. Similar analysis will be performed to compare urinary sodium and phosphate assays in spot and 24 hour urine specimens.

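### The protocol claims 80% power on 1968 evaluable and 2255 total participants, but its own summary gives 1822 subjects, which by the same method supports about 71–77% power

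*Protocol*

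**What the plan says.** Section 8.1 (Sample Size Determination) takes its inputs from two published risk-score studies: "Based on these studies the smaller event rate was 12% and the smallest significant Hazard Ratio was 1.2". It continues: "Therefore the total sample size for this study, using the Cox Proportional Hazards models with Power 80% and at significant level 5%, is 1968". It then allows for losses: "Assuming death rate during the 5 years of 3% and drop out rate of 10% the final total sample is 2255". Recruitment is planned over one year at about 190 participants per month, which fits a target near 2255.

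The Study Summary of the same protocol version (2.3, October 2013) gives 1822 under the number of subjects.

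Section 8.2 (Statistical Methods) states the analysis that the sample is meant to support: "Cox proportional hazards models will be used to identify independent baseline risk factors for CKD progression and cardiovascular events at 5 and 10 years". The resulting coefficients are to feed a risk score.

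**The concern.** One version of the protocol carries two cohort sizes, and the power statement belongs to the larger one. The summary figure is below the inflated total and also below the number that section 8.1 says must be evaluable before any allowance for death or drop-out. The stated 80% therefore cannot hold for 1822 participants on the protocol's own inputs, and no section says what power remains.

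Finding risk factors is the central purpose of the study. A reader who takes section 8.1 at face value would credit the cohort with more sensitivity at a hazard ratio of 1.2 than it has, and could read too much into a null result for a factor of about that strength.

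**Working it through.** **Inputs from section 8.1:** hazard ratio 1.2, event rate 12%, power 80%, significance level 5%, deaths 3%, drop-out 10%. **From the Study Summary:** 1822 subjects. **Inferred, because not stated:** two-sided test; hazard ratio per standard deviation of one continuous covariate (SD = 1); no correlation with other covariates (R² = 0).

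**1. Reproduce the plan's figures.** For a Cox model with one standardised covariate, the events required are

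D = (z₀.₉₇₅ + z₀.₈₀)² / (ln HR)² = (1.960 + 0.842)² / (ln 1.2)² = 7.849 / 0.03324 = 236.1.

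- Evaluable participants: 236.1 / 0.12 = 1967.7, against the stated 1968.
- Total: 1968 / (0.97 × 0.90) = 2254.3, against the stated 2255.

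Other readings tried do not fit. A one-sided 5% test needs 186 events and 1550 participants. A binary factor split 50:50 needs 945 events and 7875 participants.

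**2. Compare with 1822.**

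- 2255 − 1822 = 433, and 433 / 2255 = 19%.
- 1968 − 1822 = 146, so 1822 falls short even before losses.

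**3. Apply the same method to 1822.** Power = Φ(√D × ln 1.2 − 1.96), and the hazard ratio detectable with 80% power = exp(2.802 / √D).

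| | Evaluable | Events at 12% | Power at HR 1.2 per SD | HR for 80% power |
|---|---|---|---|---|
| Both losses removed in full | 1822 × 0.97 × 0.90 = 1591 | 190.9 | Φ(0.1823 × 13.82 − 1.96) = 71% | exp(2.802 / 13.82) = 1.225 |
| No losses | 1822 | 218.6 | Φ(0.1823 × 14.79 − 1.96) = 77% | exp(2.802 / 14.79) = 1.209 |

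**4. What would move these figures.**

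- *Downward:* correlation of the factor with other covariates multiplies the effective number of events by (1 − R²). The protocol gives no R². For assumed values of 0.1, 0.2 and 0.3, power is 67%, 62% and 56% after losses, or 72%, 67% and 62% with none. Only the direction is certain; the sizes are illustrations.
- *Upward:* a higher cumulative event rate. Recovering 236.1 events needs 236.1 / 1591 = 14.8% after losses, or 236.1 / 1822 = 13.0% with none. Follow-up runs to 10 years, but section 8.1 gives no 10-year rate.

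**The case against.** The strongest reply has four parts.

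- **The calculation is correct and is written as a prior estimate.** This stands. Both figures reproduce, so the fault is an inconsistency between sections and not an arithmetic error. There is no reason to delete the planning rationale.
- **71% is the low end.** This stands. It discards everyone who dies or drops out. Section 8.3 keeps their data up to death or withdrawal, section 4.3.2 seeks permission to go on collecting outcomes after withdrawal, and some deaths are themselves cardiovascular endpoint events under section 3.2. A range of 71% to 77% is the fair statement, and its upper end is still below 80%.
- **Ten-year follow-up could supply the missing events.** It could, but the protocol gives no 10-year rate, and the death rate used in section 8.1 is for 5 years.
- **1822 may not be the final enrolment.** The summary only labels it the number of subjects. The version date and the year-5 funding already obtained suggest that recruitment had closed, but no section says so. If 1822 is a target instead, it contradicts 2255 just as directly.

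A reader might also infer three stronger points that the document does not support.

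- *That power is far lower because the models contain binary factors such as sex and diabetes.* Section 8.2 names no covariates for the Cox models. Sex and diabetes appear there only as subgroups for comparing eGFR equations, and section 8.1 makes no claim about a binary contrast.
- *That the Background disowns the source of the 12% rate.* It says of earlier scoring systems that "these studies have largely been limited to patients with specific kidney diseases and have not been validated in more general populations of patients with CKD". That concerns validation of the scores; it does not say that the event rate cannot be carried over. Section 8.1 also took the smaller of the available rates.
- *That the true event rate is well below 12%.* The protocol gives no lower figure.

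**Conclusion.** The inconsistency is real. Section 8.1 attaches 80% power at a hazard ratio of 1.2 to 1968 evaluable and 2255 total participants, while the same version reports 1822 subjects. By the method that reproduces the protocol's own figures, 1822 gives 71% power after the stated losses and 77% with none, so the stated 80% is not met in either case. The effect detectable with 80% power rises from 1.20 to about 1.21–1.225.

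This rests on the 12% event rate and on the inferred two-sided test, per-SD scaling and zero covariate correlation. Correlation among covariates in the multivariable models would lower power by an amount the protocol does not let one compute.

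The point is moderate. The power statement should be corrected, but the loss in detectable effect is small, and no endpoint, analysis or participant procedure is affected. It would go too far to conclude that the sample size was miscalculated or that the cohort cannot serve its purpose.

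**What to change.** In section 8.1:

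1. Say how 1822 relates to 2255: whether it is the number enrolled or a revised target.
2. Keep the 1968 and 2255 calculation, labelled as the planning target, and state its assumptions (two-sided 5%, hazard ratio per standard deviation of a single covariate, no allowance for covariate correlation), once the sponsor has confirmed them.
3. Add a statement along these lines: *With 1822 participants and a 12% event rate, about 191 events are expected after 3% deaths and 10% drop-out, or about 219 with no losses. Power for a hazard ratio of 1.2 per standard deviation is then about 71% to 77% before adjustment for other covariates, and 80% power is available for a hazard ratio of about 1.21 to 1.225. Correlation among covariates in the multivariable models will lower this; additional events by 10 years could raise it.*

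The cost is a few sentences and a less favourable power figure. No change to enrolment, endpoints or analyses is needed.

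### Protocol section 8.1 attaches 80% power to a urine sub-study size of 160 that works as a precision-only calculation, and the 80% does not follow from it

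*Protocol*

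**What the plan says.** Protocol section 8.1 (Sample Size Determination) gives a separate sample size for "the sub-study comparing spot early morning urine biochemistry with that from 24hour urine collections". It says that "a sample of 160 would allow us to show a correlation co-efficient of 0.9 with precision of the estimate of 0.03 at 80% power" and adds a 5% significance level, citing previously published data. It does not say which correlation coefficient is meant, what the null value is, whether the test is one- or two-sided, or whether precision means the half-width of a confidence interval.

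Section 8.2 (Statistical Methods) describes the analysis: "Intraclass Correlation Coefficients will be used for comparing the three methods and Bland-Altman plots will be performed". It also says that "24 hour urinary protein will be the standard against which the other methods are compared". A similar analysis is planned for sodium and phosphate in spot and 24-hour specimens.

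**The concern.** Precision and power answer different questions. A precision target fixes the expected width of an interval. Power is the probability of rejecting a stated null value, or, in the assurance sense, the probability that the achieved interval is narrow enough. Section 8.1 puts both in one sentence with one sample size. If 160 comes from the precision target alone, the 80% describes nothing that was calculated.

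The sub-study bears on whether spot urine tests can stand in for 24-hour collections, and section 2 lists assessing the value of monitoring urine albumin to creatinine ratio, sodium and phosphate among the objectives. The section invites a reader to take 80% as the chance of achieving the stated result.

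**Working it through.** **Inputs.** From section 8.1: n = 160, r = 0.9, precision 0.03, power 80%, significance 5%. Assumptions, because the protocol is silent: precision is the half-width of a 95% interval; where a null is needed, it is 0.9 − 0.03 = 0.87; both one- and two-sided tests are tried.

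**1. Reproducing 160 without power.** On the Fisher z scale:
- atanh(0.9) = 1.472 and SE = 1/√(160 − 3) = 0.0798.
- 95% interval: tanh(1.472 ± 1.96 × 0.0798) = tanh(1.472 ± 0.1564) = 0.866 to 0.926.
- Half-width: 0.0301. It first falls to 0.03 at n = 161.

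Two other precision formulas land close by. The large-sample SE gives n = (1.96 × 0.19/0.03)² ≈ 154. Bonett's formula for an intraclass correlation (ICC) of k methods, with full interval width w = 0.06, is n = 8z²(1 − ρ)²[1 + (k − 1)ρ]²/[k(k − 1)w²] + 1, which gives about 155 for k = 2. For k = 3 the same formula gives about 113. So 160 matches a precision calculation for two methods, with no power term.

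**2. Reading the 80% as the chance of reaching the precision.** Simulating the sampling distribution at a true value of 0.9, the probability that the achieved 95% half-width is at most 0.03 with n = 160 is 0.51, both for a plain correlation and for a two-method ICC. It is 0.56 if the large-sample SE is used. Reaching 80% takes about 197 patients.

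**3. Reading 0.03 as the distance to a null of 0.87.**
- atanh(0.87) = 1.333, and (1.472 − 1.333)/0.0798 = 1.743.
- Two-sided 5%: Φ(1.743 − 1.96) = 0.41 by formula, 0.43 by simulation; a two-method ICC gives 0.42.
- One-sided 5%: Φ(1.743 − 1.645) = 0.54 by formula, 0.55 by simulation.
- For 80% power: 409 patients two-sided, 323 one-sided.

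**4. Joint three-method ICC.** With k = 3, n = 160 and a true value of 0.9, intervals were simulated from the F distribution on n − 1 and n(k − 1) degrees of freedom.

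| Quantity at n = 160 | Two methods | Three methods jointly |
|---|---|---|
| P(half-width ≤ 0.03) | 0.51 | 0.93 |
| Power against 0.87, two-sided 5% | 0.41–0.43 | 0.54–0.55 |
| Power against 0.87, one-sided 5% | 0.54–0.55 | 0.66–0.67 |
| n for 80% probability of half-width ≤ 0.03 | about 197 | about 141 |

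No cell in the first three rows is 80%, and neither size in the last row is 160.

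**5. What 160 does support at 80% power.** For a pairwise correlation, two-sided 5%, the null that can be excluded is tanh(1.472 − 2.80 × 0.0798) = 0.848. At the rounder value of 0.85: atanh(0.85) = 1.256, (1.472 − 1.256)/0.0798 = 2.71, and Φ(2.71 − 1.96) = 0.77.

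**The case against.** The strongest objection is that section 8.1 names no particular coefficient, while section 8.2 says that "Intraclass Correlation Coefficients will be used for comparing the three methods". If that means one ICC across three methods, 160 patients give about 93% probability of the stated precision, which is better than 80%. This stands as a limit on the point. A reader might infer that the 80% fails on every reading, that it is overstated by 30 to 40 percentage points throughout, or that the lower limit will fall below 0.87 more often than not. The documents do not support those statements without conditions: they hold for a pairwise coefficient, and the last one reverses for a joint three-method ICC. The pairwise case is still the natural one. Section 8.1 speaks of spot against 24-hour urine, section 8.2 makes the 24-hour measure the reference, and sodium and phosphate have only two methods to compare.

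The null of 0.87 is not in the protocol. On the plain meaning of precision, 160 is right and only the added power clause is unsupported. That is fair, and it is why the figures against 0.87 are conditional here.

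Some three-method variants come near. A two-sided test of 0.90 against 0.93 needs 166 patients and has 78.6 to 79.1% power at 160. The probability that the lower limit lies within 0.03 of the estimate is 76% at 160. Neither returns 160 at 80%, and the text describes neither.

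A reader might also count the absence of a written hypothesis test in section 8.2 as a fault. It is not one here, because that detail may sit in a statistical analysis plan that is not shown. Nor can the published data behind the calculation be seen, so the account of how 160 arose is an inference from a close numerical match.

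**Conclusion.** The point holds in a limited form and is minor. Section 8.1 states a definite power that its own inputs do not yield. The 160 agrees with a 95% half-width of 0.03 at a correlation of 0.9 without any power term. In the pairwise comparison, the quantity nearest to the stated 80% is a 51% chance of achieving that half-width. Figures against 0.87 are lower two-sided and similar one-sided, but rest on a null chosen for this check. Under a joint three-method ICC the result is above 80% for precision and below it for power against 0.87.

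These results assume a true value of 0.9, bivariate normal data for the plain correlation, and a one-way F model for the ICC. A reader might infer that the sub-study is too small and should grow to about 200 or 400 patients. The documents do not support that: 160 meets the precision target in expectation, and no test against 0.87 is planned.

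**What to change.** Keep 160. In section 8.1, remove the clause "at 80% power with a significance of 5" per cent, and say instead that with 160 patients and a true pairwise correlation of 0.9 between spot and 24-hour measurements, the expected 95% confidence interval is about 0.87 to 0.93 (half-width about 0.03).

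If the sponsor prefers to keep a power figure, the sentence should name the coefficient, the null value and the sidedness, and give the power that holds. For a pairwise correlation at two-sided 5%, that is 80% against 0.848, or about 77% against 0.85. If the joint three-method ICC is the intended coefficient, say so and recompute the expected interval for it.

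The cost is one corrected sentence. No patients, measurements or analyses change; the sub-study merely loses a power claim it cannot support.
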